### Study procedures

The study flow chart is presented in Fig. 1. It is planned to include the 120 women in 2 years (concordant with the number of patients yearly treated in Clinique Pasteur) and the end of the study is anticipated for the end 2019.

**Fig. 1 Fig1:**
[figure not shown]
BACCARAT study flowchart

Each patient is included at baseline before RT and followed for 2 years post radiotherapy.At baseline, before RT, in addition to classical care, patients have cardiology consultation including description of potential cardiovascular risk factors; 2D-speckle-tracking echocardiography (see Table 2) and Coronary computed tomography angiography (see Fig. 2) are performed; specific blood sample for biomarkers analysis is collected (see the list of biomarkers in Table 3).At the end of RT another specific blood sample for biomarkers analysis is collected.Six month after RT another specific blood sample for biomarkers analysis is collected and 2D-speckle-tracking echocardiography is performed.Two years after RT corresponding to the end of follow-up, a last blood sample for biomarkers analysis is collected; 2D-speckle-tracking echocardiography and Coronary computed tomography angiography are performed.

**Table 2 Tab2:** Echocardiographic measurements in BACCARAT protocol

- Left Ventricular Ejection Fraction measured using Simpson’s biplane method
- Left ventricular end-diastolic volume measured using Simpson’s biplane method
- Left ventricular end-systolic volume measured using Simpson’s biplane method
- Left ventricular end-diastolic diameter measured using M-mode
- Left ventricular mass measured according to ASE/EAE guidelines
**- Global and segmental longitudinal strain**
**- Global and segmental longitudinal strain rate**
- Global and segmental radial strain rate
- Global and segmental radial strain rate
- E/A wave ratio
- E/Ea wave ratio (lateral annulus)
- TAPSE (tricuspid annular plane systolic excursion)
- Tricuspid annular S wave
- Systolic pulmonary arterial pressure (based on a measure assuming a right atrial pressure of 5 mmHg)
- Left ventricular outflow tract diameter
- Left ventricular outflow tract velocity time integral
- Heart rate
- Cardiac output measured by multiplying heart rate by stroke volume

Bold data are major index taken into account for subclinical cardiac event

**Fig. 2 Fig2:**
[figure not shown]
15 segments of coronary arteries. LM: Left main coronary artery; LAD: left anterior descending artery; LCX: left cicumflex artery; RCA: right coronary artery. For each segment, the following index are measures: stenosis in % narrowed; presence of calcification; presence of soft plaque (adapted from [41])

**Table 3 Tab3:** List of circulating biomarkers measured in BACCARAT protocol

Classical biomarkers of cardiac injury
C-reactive protein, Troponin I, B-type natriuretic peptide (NT-Pro BNP), beta2-Microglobulin, Galectin 3
Inflammatory cytokines:
Interleukin 6, Interleukin 8, Interleukin 18, TNF-α
Endothelial activation and dysfunction
sVCAM,-1, s-ICAM-1, E-selectin, P-selectin, vWF, PAI-1, Fibrinogen, Thrombomoduline, TGF-β1
Microparticles
CD14(monocytes), CD31(endothelial), CD41(platelets), CD3(lymphocyte), CD235a (erythrocyte)
microRNAs
miR-1, miR-133, miR-208, miR-499, miR-126, miR-130, miR-145, miR-181, miR-150, miR-155, miR-223, miR-17, miR-18, miR-22, miR-34, miR-92, miR-140, miR-182, miR-199, miR-423, miR-590.

### Study endpoints

The primary endpoint is a subclinical cardiac outcome defined as follows: between baseline (before RT) and 2 years post RT, a decrease in the global and segmental longitudinal strain or strain rate measured by 2D-STE of at least 5 % and/or an increase in the number of coronary segments containing any plaque measured by CCTA of at least 15 %. These average percentages were chosen based on those observed in previous studies and can be considered clinically pertinent [17, 34–37].

The secondary endpoints are:Decrease in the strain or strain rate between measurements made before RT and 6 months after RT.Modified series of biomarkers between the measurements before RT and: just after RT, 6 months after RT, 24 months after RT.Correlation between the absorbed radiation dose to the whole heart and different structures of the heart and measurements of strain and strain rate and number of coronary segments containing any plaque measured 2 years after RT.

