### Planned analysis

A strength of the study is that each patient will her own control (unexposed status before RT) and evaluations will be based on individual changes of measurements over time. Paired tests for comparisons will be used. All tests will be bilateral with alpha = 5 %. Patients’ baseline characteristics before RT (pre-RT) will be used as "reference" values.(o) Description of the population at baseline (before RT) will be performed including: the medical data collected in the questionnaire, in particular the risk factors for cardiovascular disease; measurements of all biomarkers; 2D-STE measurements including strain and strain rate; CCTA measurements including mean number of coronary segments with plaques. Descriptive statistics (means, standard deviations, percentages and confidence intervals of 95 %) will be used the whole cohort.(i) For the analysis of primary endpoint, the occurrence and progression of early subclinical cardiac lesions will be analyzed based on prevalence study and Chi-square tests.(ii) Wilcoxon tests for paired-samples will be used to study the variations of targeted circulating biomarkers during follow-up. Crude temporal trends will also be considered.(iii) A detailed dose reconstruction will be performed for each woman. CT images used for treatment planning allow delineation of the heart and surrounding organs. However, on these images the coronary arteries are not visible and cannot be delineated. Registration of the planning and coronary angiography CT images will allow delineation of the coronary arteries on the planning CT images. Using the 3D dose matrix associated with the RTDose file generated during treatment planning [38] and the added coronary contours, dose volume histograms and 3D dose maps [28] of the whole heart and coronaries will be generated. This process will be performed with the Isogray treatment planning software (http://www.dosisoft.com/en/rt-planning/tps-isogray/dose-calculation-models.html). A description of the doses thus obtained will be shown for the whole cohort of women.(iv) Spearman correlations will provide results on the association between measurements of strain and strain rate and indices of coronary plaques and the measurement of biomarkers and the radiation dose absorbed by the different structures of the heart. Dose-response relationship between subclinical and dosimetric data will be studied in order to provide results on the effect of dose on subclinical outcome. These relationships will be established from coarse to fine levels, considering first the heart as a whole and going through different substructures. Logistic regression models as well as generalized linear model and repeated data models could be used for the study of the variation between 0 and 2 years the intermediate measurements.(v) For individualized risk for each patient, multivariate model of normal tissue complication probability (NTCP), which takes into account relationships among all parameters will be proposed based on subclinical cardiac lesions occurrence, including clinical, biological and dosimetric data using logistic regression and forward variable selection.

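### The dose-response secondary endpoint is worded on 2-year levels without the baseline value, while objective IV and the analysis section speak of change from before radiotherapy

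*Protocol article*

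**What the plan says.** All references are to the protocol article.

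- **Study endpoints, third secondary endpoint.** It is defined as "Correlation between the absorbed radiation dose to the whole heart and different structures of the heart" on one side and "measurements of strain and strain rate and number of coronary segments containing any plaque measured 2 years after RT" on the other. Neither a baseline value nor a change appears in it.
- **Study endpoints, other endpoints.** The primary endpoint is a change, "between baseline (before RT) and 2 years post RT, a decrease in the global and segmental longitudinal strain or strain rate", with a matching rise in plaque segments. The first secondary endpoint is also a change, "Decrease in the strain or strain rate between measurements made before RT and 6 months after RT". The biomarker endpoint likewise compares later samples with the sample before radiotherapy.
- **Secondary objectives, objective IV.** The dose-response aim is set for subclinical cardiac changes in relation to absorbed dose.
- **Planned analysis, opening.** It states that "evaluations will be based on individual changes of measurements over time", with values before radiotherapy as the reference.
- **Planned analysis, item (iv).** "Spearman correlations will provide results on the association between measurements of strain and strain rate and indices of coronary plaques", together with biomarkers and dose. The sentence gives no time point, change or adjustment. The item then says that dose-response for the subclinical outcome will be studied. It adds, as a possibility only, logistic, generalized linear and repeated-data models for the variation between 0 and 2 years.
- **Study procedures.** At baseline, "2D-speckle-tracking echocardiography (see Table 2) and Coronary computed tomography angiography (see Fig. 2) are performed". Both examinations are repeated at 2 years.

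**The concern.** The endpoint that serves objective IV measures a level, while the objective and the general rule of analysis concern change. A woman's plaque count or strain at 2 years largely reflects what she had before treatment. Leaving that out has one certain and one possible consequence. It adds variation unrelated to dose, which weakens the dose-response estimate whenever baseline and 2-year values are correlated. It could also bias the estimate, because dose is not randomised: under Study design and population it follows treated side, internal mammary treatment, heart position and selective breath-hold gating. If any of these is associated with strain or plaque before radiotherapy, the level analysis would count that association as a dose effect.

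**Working it through.** **The plan's own figure.** No sample size is stated for this endpoint. The total of 120 can be reproduced from the strain inputs in Sample size calculation (mean −16.5, SD 2.1, 5 % relative change, two-sided alpha 5 %, power 80 %):

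- n = 2 × (1.960 + 0.842)² × 2.1² / 0.825² ≈ 102.
- 102 / 0.85 = 120, allowing for the 10 % and 5 % losses given there.

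This is the formula for one group of a two-sample comparison, or for a paired comparison with zero before/after correlation. It therefore gives no planning value for that correlation. It is used here only for the number evaluable, about 102. With 102 women, the smallest correlation detectable with 80 % power is about 0.27 (Fisher z).

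**How much of the 2-year value precedes treatment, from the planning figures.**

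- Plaque: targeted rise 0.15 × 2.1 = 0.315 segments. At that target, 2.1 / 2.415 = 87 % of the mean 2-year count was there before radiotherapy.
- Strain: targeted change 0.05 × 16.5 = 0.825, against a between-woman SD of 2.1, so 0.825 / 2.1 ≈ 0.4 SD.

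**Precision.** Let ρ be the correlation between baseline and 2-year values. The documents do not give it, so it is assumed. If dose is unrelated to baseline, adjustment in a linear model leaves residual variance 1 − ρ², so the unadjusted residual variance is 1/(1 − ρ²) times larger:

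- ρ = 0.5: 1/0.75 = 1.33.
- ρ = 0.7: 1/0.51 = 1.96.

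Power follows from Fisher z with 102 women and an assumed standardised dose slope of 0.275. The correlation is 0.275/√(1 + 0.275²) = 0.265 for the level, 0.275/√(1 − ρ² + 0.275²) for the adjusted analysis, and 0.275/√(2(1 − ρ) + 0.275²) for the change score.

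| ρ (assumed) | 2-year level | Change score | Baseline-adjusted |
|---|---|---|---|
| 0.3 | 77 % | 63 % | 80 % |
| 0.5 | 77 % | 77 % | 87 % |
| 0.7 | 77 % | 93 % | 96 % |

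**Bias, conditional on a dose–baseline correlation g.** The documents do not give g either. With no true dose effect, the level correlation is expected to be ρ × g. The false-positive rates below come from simulation (102 women, 4000 runs per setting; Spearman for level and change, linear partial correlation for the adjusted analysis; nominal rate 5 %).

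| g | ρ | 2-year level | Change score | Baseline-adjusted |
|---|---|---|---|---|
| 0.1 | 0.5 | 7 % | 8 % | 5 % |
| 0.1 | 0.7 | 10 % | 6 % | 5 % |
| 0.2 | 0.5 | 16 % | 15 % | 5 % |
| 0.2 | 0.7 | 27 % | 11 % | 5 % |

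For scale: with the stated 80/20 split by side, a left–right baseline difference of d SD has correlation 0.4d/√(1 + 0.16d²) with side. That is 0.08 at d = 0.2 and 0.20 at d = 0.5. A g of 0.2 arising from side alone would need a half-SD difference before treatment.

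**Limit of the simulation.** It lets dose relate to the observed baseline. If dose instead relates to the true baseline and the baseline is measured with error, adjustment leaves roughly (1 − reliability) of the bias. A change score removes the bias in that case if true change does not itself depend on true baseline. Neither analysis is best under every assumption.

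**The case against.** The strongest reply is that the plan as a whole does use baseline. Objective IV is framed on changes, and Planned analysis opens with a change-based rule. Item (iv) commits to studying dose against the subclinical outcome, which Study endpoints defines as a change. This stands: a reader might infer that the dose-response work ignores baseline altogether, and the documents do not support that. It does not settle the point, because the commitment concerns a threshold-defined outcome, the change models are optional, and the separately listed endpoint on the measurements themselves still names 2-year values.

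Second, a reader might take the Spearman step to be fixed on 2-year values. It is not. That sentence gives no time point and, under the opening rule, its measurements could be read as changes. The timing comes only from the endpoint definition. What remains is that the step does not say which is meant.

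Third, the size of the loss is assumed. A correlation higher than those shown would give a more striking factor, but the documents supply none. Table 1 also excludes women with baseline strain above −16 %, close to the planning mean of −16.5 %. That narrows baseline strain and would tend to lower its correlation with the 2-year value. The variance factor is also exact for a linear slope and only a guide for Spearman. These limits stand. The exclusion does much less for plaque, since only CCTA findings that need therapeutic management are excluded.

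Fourth, a reader might conclude that the dose correlation will be spurious. The documents show no association between dose and baseline strain or plaque. Without one, the level correlation is less precise but not spurious.

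**Conclusion.** The point holds as an inconsistency in how one secondary endpoint is defined, with a cost if it is followed as written. The article does not fix any dose-response analysis of the continuous measures that uses baseline. The loss of precision is moderate: at assumed correlations of 0.5 and 0.7, residual variance is 1.3 and 2.0 times larger than with adjustment. In the worked example, power is 77 % against 87 % and 96 %. Bias is a possibility that depends on an unreported dose–baseline association. The definition of the primary endpoint is not affected. The amendment is worth making because it aligns the endpoint with the plan's own objective and uses data already in hand.

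**What to change.** - **Study endpoints:** redefine the third secondary endpoint as the association of absorbed dose with the 2-year value of strain, strain rate and plaque-segment count, each adjusted for the same measure at baseline. Use a regression model, or a partial Spearman correlation given baseline if a rank measure is preferred.
- **Planned analysis, item (iv):** state that this analysis will be done, and say which time points the Spearman correlations use.
- **Sensitivity analysis:** report the association of dose with change from baseline alongside, because baseline measurement error can leave residual bias after adjustment. An unadjusted change score should not be the main analysis by default, since it is less precise than the level when ρ is below 0.5.

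The cost is a few sentences and slight extra analysis. No visit, examination or participant is added, because baseline echocardiography and CCTA are already part of the study procedures.

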### Sample size calculation

The sample size was based on a statistical power of 80 %, an alpha-risk of 5 %, the definition of the primary endpoint (a decrease in the global and segmental longitudinal strain or strain rate of at least 5 % and/or an increase in the number of coronary segments containing any plaque of at least 15 %). Baseline measurements were collected from previous publications:Mean global longitudinal strain before RT [36]: −16.5 % ± 2.1 %.Mean global longitudinal strain before RT [36]: −1.00/s ± 0.13/s.Number of segments with coronary plaques [37]: 2.1 ± 1.0 segments.

Taking into account tailed test for comparisons, but also exclusion criteria (±10 % of women whose echocardiography or CCTA at baseline may be abnormal and require therapeutic management and should be excluded; ± 5 % of women may resort to cardiotoxic chemotherapy during the 2 year follow-up and should also be excluded; less than 1 % of women likely to die within 2 years after RT - these women will be analyzed until the date of death), the inclusion of 120 women is necessary.

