#### Echocardiography and myocardial changes

Cardiac echography can be used to evaluate myocardial dysfunction. Global Longitudinal Strain and strain rate (GLS) assessed using automated 2D-speckle-tracking echocardiography (STE) is a recent technique for detecting and quantifying subtle disturbances in Left ventricular (LV) systolic function. This technique is operator independent, more reproducible than ejection fraction (EF) and GLS was shown to be a superior predictor of cardiac events compared to EF. In particular, this method was used in the context of cardiotoxicity after breast RT. In Belgium, two prospective studies were based on measurements of strain and strain rate as an indicator of myocardial contractility [10, 11]. Comparing the strain before breast radiation, then a few months later, both studies showed significant changes related to radiotherapy. The most recent study included 51 women treated for left breast cancer and 24 women treated for right breast cancer. Both strain and strain rate were significantly decreased (mean 5 %) during the first year following RT for left-sided patients: a decrease in strain was observed at all post-RT time points (−17.5 ± 1.9 % immediately after RT, −16.6 ± 1.4 % at 8 months and −17.7 ± 1.9 % at 14 months vs −19.4 ± 2.4 % before RT, *p* < 0.01). Similar results for longitudinal strain decrease were also observed in a recent German study [12]. Based on this clinical state, it appeared that early cardiotoxicity of radio-induced breast RT could be measured based on subclinical myocardial functional changes which is concordant with recent publication of recommendations in the evaluation of cardiovascular complications after radiotherapy in adults including in particular cardiac echography examination [13]. However these results on strain and strain rate remain to be confirmed and more precise analyses depending on the dose distribution over the surface of myocardial could enable a better understanding of a possible dose response.

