• Age between 50 and 70 years • Women surgically treated for left or right breast cancer and for whom adjuvant treatment is radiotherapy with irradiation of the breast or chest wall irradiation and possibly ganglion chains, • Adjuvant radiotherapy with 3D CRT performed in Clinique Pasteur Toulouse • WHO performance status ECOG (Eastern Cooperative Oncology Group - index usually used to describe the patient's condition) = 0 or 1 • Being volunteer to participate in the study and having signed the consent form	• Indication of adjuvant chemotherapy • Clinically or radiologically detectable metastasis • Personal history of coronary artery disease or myocardial disease • Personal history of breast cancer or other cancer requiring radiotherapy to the thorax • Patient with controlled infection or severe disease and/or non-hazardous to their participation in the study • Contraindications to injection of iodinated contrast (for CCTA): pregnancy, renal failure, allergy • Pregnancy, lactation • Abnormal echocardiography before radiotherapy: - LVEF <50 % - Longitudinal strain > − 16 % - Longitudinal strain rate <1 %/s - Abnormal wall motion • CCTA before radiotherapy showing that therapeutic management is required (by decision of the radiologist and cardiologist)

*3D CRT* 3D conformal radiation therapy, *WHO* World Health Organisation, *CCTA* coronary computed tomography angiography, *LVEF* left ventricular ejection fraction

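### The sample-size inputs, the Table 1 strain cut-off and the 10 % baseline-exclusion allowance do not fit together, so the 120 women and 80 % power are not supported as written

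*Protocol article*

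**What the plan says.** All places are in the protocol article.

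- **Sample size calculation, targets.** "The sample size was based on a statistical power of 80 %, an alpha-risk of 5" per cent, for a relative fall of 5 % in strain or strain rate and/or a relative rise of 15 % in plaque-bearing coronary segments.
- **Sample size calculation, inputs.** "Baseline measurements were collected from previous publications": strain −16.5 ± 2.1 %, and a second line of −1.00 ± 0.13/s. The second line is also labelled as strain, though its unit is that of strain rate.
- **Sample size calculation, losses.** About 10 % for "women whose echocardiography or CCTA at baseline may be abnormal and require therapeutic management and should be excluded", about 5 % for cardiotoxic chemotherapy during follow-up, and under 1 % deaths, which stay in the analysis until death. With these taken into account, the section arrives at 120.
- **Table 1, exclusion criteria.** "Abnormal echocardiography before radiotherapy" covers LVEF below 50 %, longitudinal strain above −16 %, "Longitudinal strain rate <1" %/s, and abnormal wall motion. A separate CCTA criterion applies where therapeutic management is required.
- **Planned analysis.** "Paired tests for comparisons will be used"; "All tests will be bilateral with alpha = 5" per cent.
- **Background, Echocardiography and myocardial changes.** A cited breast-radiotherapy series had pre-treatment strain of −19.4 ± 2.4 % in left-sided patients, in whom "a decrease in strain was observed at all post-RT time points". The sample-size section does not use this figure.

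**The concern.** The strain cut-off lies almost on the assumed mean, so a large share of the assumed population would be screened out. The allowance for that is about 10 %, and it must also cover CCTA, LVEF, wall motion and strain rate. If the allowance is built into the 120, then the number evaluable, the effect in strain points and the SD behind the stated power describe a population that the entry criteria do not admit.

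The strain-rate criterion is a separate problem of wording. Table 1 gives a positive limit in %/s, while the sample-size input is negative and in 1/s. The article says that recruitment is under way, so the reading chosen bears on current eligibility decisions.

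**Working it through.** **1. Reproduce the 120.** The article gives no formula. A two-sided 5 % test with 80 % power has (1.960 + 0.842)² = 7.849. The 5 % effect on strain is 0.05 × 16.5 = 0.825 points.

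- n = 2 × 7.849 × (2.1/0.825)² = 101.7, so 102 evaluable.
- 102/(1 − 0.10 − 0.05) = 102/0.85 = 120. Compounding the losses, 102/(0.90 × 0.95) = 119.3, also gives 120.

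The match is exact, so the 10 % appears to be inside the 120. The formula equals a before/after comparison with zero within-patient correlation (SD of change = √2 × 2.1).

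**2. Share beyond the strain cut-off, assuming normality.**

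- Distance from mean to cut-off: (−16 + 16.5)/2.1 = 0.238 SD.
- P(strain > −16 %) = 1 − Φ(0.238) = 40.6 %. Rounding of the inputs gives 39.4 % to 41.7 %.
- With SD 2.1, a 10 % loss on strain alone would need a mean of −16 − 1.2816 × 2.1 = −18.7 %.

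**3. Evaluable women if 120 is counted before baseline exclusions.** 120 × 0.594 × 0.95 = 67.7, about 68, against 120 × 0.85 = 102.

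**4. Baseline strain of the women who pass.** For N(−16.5, 2.1) truncated to −16 or below, φ(0.238)/Φ(0.238) = 0.3878/0.5941 = 0.653.

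- Mean = −16.5 − 2.1 × 0.653 = −17.9 %.
- SD = 2.1 × √(1 − 0.238 × 0.653 − 0.653²) = 1.36 %.

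**5. What 68 evaluable women would mean for power** (0.825-point effect and SD 2.1, without truncation).

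- Correlation 0: about 63 %.
- Correlation 0.5: about 90 %; 51 women would be enough.

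With truncation of the baseline only and correlation 0, the SD of change is √(1.36² + 2.1²) = 2.50 and the 5 % effect is 0.05 × 17.87 = 0.894. Then n = 7.849 × (2.50/0.894)², about 62, setting regression to the mean aside.

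**6. The background series as a sensitivity value.** (−16 + 19.4)/2.4 = 1.417 SD, and 1 − Φ(1.417) = 7.8 % beyond −16 %, on strain alone and in left-sided patients.

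**7. Strain-rate criterion against the input of −1.00 ± 0.13/s.**

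- Signed values: every woman is below +1, so all are excluded.
- Magnitude in %/s as printed: 1 %/s = 0.01/s, which is (1.00 − 0.01)/0.13 = 7.6 SD below the mean, so essentially none are excluded.
- Magnitude in 1/s: the cut-off equals the assumed mean, so about 50 % are excluded. No section states this reading.

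**The case against.** - **The 10 % may cover only women who need therapeutic management.** The wording allows that. In Table 1, however, the echocardiographic limits exclude on their own, and only the CCTA criterion mentions management. On this narrow reading, exclusions on the cut-offs are not allowed for at all.
- **The 120 may be counted after screening.** The section counts these exclusions in reaching 120, and Study procedures has each patient included at baseline. Even on the other reading, the women entered would not have the assumed mean and SD.
- **Normality is not stated.** This stands as a qualification. A mean of −16.5 and SD of 2.1 can be built with only 10 % beyond the cut-off (10 % at −10.2 and 90 % at −17.2), though such a distribution is implausible for strain.
- **The cited series may not represent the women screened here.** That is possible, but it is the series on which the plan bases its number.
- **The cohort may still have enough power.** This stands. A reader might infer that 120 is too small and should become 102/(0.594 × 0.95) = 181. The documents do not support that step. It keeps a correlation of zero and an untruncated SD, while the plan specifies paired tests and gives no correlation. The calculations above show needs of 51 or 62 under other assumptions, both below 68.
- **A reader might also add a 50 % loss on strain rate.** That rests on the reading in 1/s, so it cannot be claimed as the plan's own figure.

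**Conclusion.** The point holds as an inconsistency among printed figures. The sizing inputs imply that about 41 % of women fail the strain criterion alone, roughly four times the allowance for all baseline exclusions together. This assumes normality and that the cited baseline describes the women screened. If the 120 includes women excluded at baseline, as the text and the reproduced arithmetic indicate, about 68 are evaluable rather than about 102. The 120 and the 80 % power are therefore unsupported as written; an underpowered cohort is not demonstrated.

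The strain-rate criterion is a second defect that does not depend on the sample size. Its sign and unit conflict with the input, whose label is also wrong, and the share excluded runs from none to all.

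**What to change.** 1. Reconcile the baseline inputs, the Table 1 echocardiographic criteria and the 10 % allowance. Which cut-off is right is for the investigators to settle.
2. State whether 120 is counted before or after baseline exclusions.
3. Use a baseline mean and SD that describe the women the entry criteria admit. Take the exclusion rate from all women screened so far, because those who passed cannot show how many fail.
4. Use −19.4 ± 2.4 % only as a sensitivity value. It is left-sided, whereas 20 % of the cohort is to be right-sided, and its 7.8 % leaves out CCTA and the other echocardiographic criteria.
5. Recompute for the paired analysis with a stated within-patient correlation and a range around it, and restate the evaluable number and the power.
6. Correct the sign, unit and label of strain rate so that Table 1 and the sample-size section agree.

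The cost is a recalculation and a wording amendment. No extra patients are requested.

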### Study design and population

BACCARAT study consists in a monocentric prospective cohort study that will finally include 120 women treated with adjuvant 3D CRT for unilateral breast cancer in the Clinique Pasteur in Toulouse, France, without chemotherapy, and followed for 2 years after RT.

In the Clinique Pasteur, there are no competing methods to 3D-CRT at the moment. All patients with breast cancer are treated with 3D-CRT and breath-hold gating is used for patients treated left breast cancer with heart very close to the anterior chest wall or for dose constraints achievement (mean heart dose < 5Gy and V25Gy < 10 %). Women aged between 50 and 70 years, for whom adjuvant 3D CRT is indicated with or without breath-hold gating, with no indication of chemotherapy are eligible for the study. Both women with left (80 % of the sample) or right (20 % of the sample) breast cancer are included. This choice to include both sides is justified by two reasons: (i) if the internal mammary chain is treated significant doses can result, whatever the treated side; (ii) if the internal mammary chain is not treated the right side treatment will provide lower doses, an important point for the dose response analysis. With this design, each patient (after RT) could be her own control (before RT). Moreover, the left-sided patients could also be compared to the right-sided patients. Inclusion and exclusion criteria are presented in Table 1.

**Table 1 Tab1:** Inclusion and exclusion criteria

Inclusion criteria	Exclusion criteria

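### Women who receive cardiotoxic chemotherapy during follow-up are excluded with no cut-off date; read plainly, this discards their valid pre-chemotherapy measurements at the end of RT and at 6 months

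*Protocol article*

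**What the plan says.** The parenthesis on exclusions in Sample size calculation lists three groups.

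- About 10 % with abnormal baseline imaging needing management, who are excluded.
- About 5 % "of women may resort to cardiotoxic chemotherapy during the 2 year follow-up and should also be excluded".
- Fewer than 1 % who die within 2 years, of whom it says "these women will be analyzed until the date of death".

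Table 1 excludes only women with an indication for adjuvant chemotherapy at entry. The rule for chemotherapy started later therefore appears only in the sample size text.

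The flow chart text under Study procedures schedules blood at baseline, end of RT, 6 months and 2 years, echocardiography at baseline, 6 months and 2 years, and CCTA at baseline and 2 years. Under Study endpoints, one secondary endpoint is "Decrease in the strain or strain rate between measurements made before RT and 6 months after RT". Another is biomarker change from baseline to three times: just after RT, 6 months and 24 months. Item (iv) of Planned analysis allows, without requiring, repeated-data models for the intermediate measurements.

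**The concern.** Starting chemotherapy during follow-up is a post-baseline event. A sample or echocardiogram taken before it starts is unaffected by the drug and is as informative about radiotherapy as any other woman's. Dropping it because of what happened later has two consequences.

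1. **Lost data.** The 6-month strain endpoint and two of the three biomarker contrasts lose usable observations.
2. **Selection on the future.** The 6-month analysis would describe only women who went on to avoid cardiotoxic chemotherapy until 2 years, a group that cannot be identified at 6 months.

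The sentence also treats two intercurrent events differently without giving a reason: follow-up is kept up to death but not up to chemotherapy.

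**Working it through.** **Step 1. Reproduce the planned number.** Inputs from Sample size calculation: power 80 %, alpha 5 %, baseline global longitudinal strain −16.5 % with SD 2.1 %, and "a decrease in the global and segmental longitudinal strain or strain rate of at least 5" %. Planned analysis adds "All tests will be bilateral with alpha = 5" %. Two inputs are assumptions: the 5 % is read as relative, and the pre/post correlation, which is not stated, is set to zero.

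- Difference: 0.05 × 16.5 = 0.825 points.
- n = 2 × (1.960 + 0.842)² × 2.1² / 0.825² = 2 × 7.849 × 4.41 / 0.6806 = 101.7, so 102 evaluable women.
- Inflation for 10 % + 5 %: 102 / (1 − 0.15) = 120.

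This gives the stated 120 exactly, with the 5 % counted as full loss from the evaluable number. It does not show which analyses the women leave: exclusion from the 2-year endpoint alone gives the same 120.

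**Step 2. Women affected.** 120 × 0.05 = 6. After baseline exclusions, 120 × 0.90 = 108. With the chemotherapy group also removed, 108 − 6 = 102.

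**Step 3. Gain at the early visits.**

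- Interval width, 108 against 102 women: √(102/108) = 0.972, about 3 % narrower.
- Power of a two-sided paired t-test for a 5 % relative strain change at zero correlation: 0.816 with 108 women, 0.794 with 102. At an assumed correlation of 0.5: 0.982 and 0.976.

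These are upper bounds. They require all six women to start chemotherapy after the visit in question, and the article gives no timing.

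**Step 4. Largest shift at 2 years.** Let f = 6/108 = 0.056 be the fraction removed, p the prevalence of the primary endpoint in those kept, and q that in those removed. Removal shifts the estimate by f × (p − q). The article gives no prevalence, so p = 0.30 and p = 0.50 are assumed, with q at its extremes.

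| p | q | shift (percentage points) |
|---|---|---|
| 0.30 | 1 | −3.9 |
| 0.30 | 0 | +1.7 |
| 0.50 | 1 | −2.8 |
| 0.50 | 0 | +2.8 |

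The 95 % half-width with 102 women is 1.96 × √(p(1 − p)/102), which is 8.9 points at p = 0.30 and 9.7 at p = 0.50. Even the extreme shifts are less than half of that.

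**Step 5. Scope of the exclusion in the text.** The word also places the chemotherapy group with women excluded at baseline, who contribute no follow-up. The next clause gives deaths an explicit end date. A woman who dies before 2 years lacks a 2-year value too, so if only that value were meant, the two groups would hardly need different wording. No other section limits the rule to the 2-year endpoint.

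**The case against.** The strongest reply is that the clause is an attrition allowance for the 2-year primary endpoint, not a definition of an analysis set. Planned analysis never removes these women from the 6-month or biomarker analyses. It describes baseline data and doses for the whole cohort, and an article may leave visit-by-visit analysis sets to a fuller document. This stands in part: removal from every analysis is an inference. But the article does state a rule, and as worded it has no limit. If 2-year exclusion alone was meant, one sentence should say so.

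Deaths and chemotherapy also differ. A woman who dies has no 2-year measurement. A woman given chemotherapy may have one, but it is confounded by a cardiotoxic drug. Keeping that value out of the main 2-year analysis is defensible. The reply does not reach measurements taken before chemotherapy.

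A reader might go further and infer that the exclusion preferentially removes women with high heart dose and so biases the dose-response, because Study design and population says "if the internal mammary chain is treated significant doses can result, whatever the treated side". The documents do not support this. Nothing ties later chemotherapy to nodal irradiation or heart dose, so no size can be calculated. Moreover, exclusion that depends on dose alone costs precision without biasing a dose-response slope. Bias would need exclusion to depend on the cardiac outcome given dose, and the article offers no such route.

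**Conclusion.** The point holds as a small improvement that needs no new data. As worded, the rule discards valid early measurements from about 6 women and selects the early-visit analyses on a future event. Keeping those measurements gives at most 108 women instead of 102 and intervals up to about 3 % narrower. This rests on the article's 10 % and 5 % allowances and on chemotherapy starting after the visit concerned. The planned 120 is unaffected, because the 2-year values of these women still do not count in the main analysis.

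It would be too much to conclude that the primary result is compromised: under the assumed prevalences the largest shift is about 4 points, against a half-width of 9 to 10. Nor does analysing up to chemotherapy remove selection at 2 years. CCTA is done only at baseline and 2 years, and the dose-correlation endpoint uses 2-year values, so women treated before that visit still leave both main analyses. A sensitivity analysis can only examine that selection.

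**What to change.** - Replace the exclusion of these women with analysis until the start of cardiotoxic chemotherapy, parallel to the rule for deaths. All earlier measurements then enter the end-of-RT, 6-month and any repeated-measures analyses.
- State that measurements after the start of chemotherapy are left out of the main 2-year analysis, and add a sensitivity analysis that includes them.
- Report the number of such women by treated side and mean heart dose, so that readers can see whether they differ from the rest.

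The cost is one sentence defining the rule, one sensitivity analysis and one descriptive table. The start date of chemotherapy must be on record. No patients, visits or procedures are added.
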